***Recombinant modified vaccinia virus Ankara as a vector***

The successful worldwide eradication of smallpox via vaccination with live vaccinia virus highlighted vaccinia as a candidate virus for recombinant use. MVA is a highly attenuated strain of vaccinia virus that is unable to replicate efficiently in human cell lines and most mammalian cells [25]. MVA underwent multiple, fully characterised deletions during more than 570 passages through chicken embryo fibroblast cells [26] including deletions in host range genes and genes encoding cytokine receptors. Viral replication is blocked at a late stage of virion assembly, so, importantly, viral and recombinant protein synthesis is unimpaired [27]. This means that MVA is an efficient single round expression vector, incapable of causing infection in mammals. Replication-deficient recombinant MVA has been seen as an exceptionally safe viral vector. It has been administered to more than 120,000 vaccinees as part of the smallpox eradication programme, with an excellent safety record, despite the deliberate vaccination of high risk groups [26]. This safety in man is consistent with the avirulence of MVA in animal models, where recombinant MVAs have also been shown to be protectively immunogenic as vaccines against viral diseases and cancer. Importantly for a

tuberculosis vaccine, recombinant MVAs expressing HIV antigens have been shown to be safe and immunogenic in HIV-infected subjects [28-30]. There is now safety data from many recombinant MVAs expressing HIV, malaria and melanoma antigens that are currently in phase I/II trials in both the UK and Africa [28-35].

### ***Clinical studies using MVA85A***

MVA85A has been administered (at a dose of  $5 \times 10^7$  pfu) to 57 healthy volunteers in the UK, 21 healthy adults and 8 healthy infants in The Gambia and 24 adults and 8 adolescents in South Africa, with no vaccine-related serious adverse events (table one). In addition to this, MVA85A low dose ( $1 \times 10^7$  pfu) and high dose ( $1 \times 10^8$  pfu) have each been given to 12 volunteers with no vaccine-related serious adverse events. All volunteers have temporary local redness with, typically, a 5mm central red area with a paler pink surrounding area that ranges in size from about 1-7mm in diameter and peaks at 48 hours post vaccination. At seven days post vaccination, generally only the central red area remains. This fades over the next few weeks and is not usually apparent at 2 months after vaccination.

There is a theoretical risk of a Koch reaction i.e. the development of immunopathology due to the stimulation of an exaggerated immune response. Boosting immunizations in individuals who have some pre-existing mycobacterial immunity may stimulate the immune response to such an extent that a Koch reaction develops. However, mouse data suggests that these reactions correlate with high mycobacterial load and are unlikely in healthy individuals, even if latently infected [36]. Our initial studies were performed in healthy volunteers with no evidence of pre-existing mycobacterial immunity, as assessed by Heaf testing and cellular immune responses to *M.tb* peptides, (PPD, ESAT 6 and CFP10), and who had not received BCG vaccination. We have now completed studies in the UK vaccinating volunteers previously vaccinated with BCG [37] and in The Gambia. These volunteers were excluded if their Heaf test was greater than grade II. A further study, involving vaccination of 12 volunteers who were latently infected with TB, is nearing completion and to date has had no vaccine-related serious adverse events. Importantly, in this study, the side effect and immunogenicity profile is the same as in previous studies and there have been no clinical, radiological or immunological signs of a Koch reaction. Phase II studies in 24 healthy *M.tb* infected adults and 12 adolescents commenced in Cape Town in August 2005 and the adult arm of this trial has now completed enrolment. Recruitment into the adolescent arm is ongoing.

**Table 1: Summary of clinical trials with MVA85A**

| Country      | Volunteer Group                                  | Dose of MVA85A                                     | Number of volunteers | Status             |
|--------------|--------------------------------------------------|----------------------------------------------------|----------------------|--------------------|
| UK           | BCG naïve and Heaf grade 0                       | 5 x 10  pfu x 2 doses                  | 14                   | Completed          |
| UK           | BCG-prime and MVA85A boost (1 month interval)    | 5 x 10  pfu                            | 10                   | Completed          |
| UK           | BCG-prime and MVA85A boost (24 month interval)   | 5 x 10  pfu                            | 5                    | Completed          |
| UK           | BCG-prime and MVA85A boost (10-20 year interval) | 5 x 10  pfu                            | 12                   | Completed          |
| UK           | BCG-prime and MVA85A dose-optimization           | 1 x 10  pfu
1 x 10  pfu | 24 (12 each dose)    | Completed          |
| Gambia       | BCG naïve and Heaf grade 0                       | 5 x 10  pfu x 2 doses                  | 11                   | Completed          |
| Gambia       | BCG-prime (birth) and MVA85A-boost               | 5 x 10  pfu                            | 10                   | Completed          |
| South Africa | BCG naïve or BCG-prime MVA85A-boost              | 5 x 10  pfu                            | 24 (12 per group)    | Enrolment complete |
| UK           | Latent infection                                 | 5 x 10  pfu                            | 12                   | Completed          |
| The Gambia   | BCG vaccinated infants                           | 2.5 and 5 x 10  pfu                    | 350                  | Recruiting         |
| South Africa | Healthy BCG-vaccinated adolescents               | 5 x 10  pfu                            | 12                   | Enrolment complete |
| UK           | Asymptomatic HIV+                                | 5 x 10  and 1 x 10  pfu    | 20                   | Recruiting         |
| South Africa | HIV+/TB-, HIV-/TB+ or HIV+/TB+                   | 5 x 10  pfu                            | 36                   | Recruiting         |

## Rationale

This study is designed to evaluate the safety of MVA85A in healthy volunteers in Senegal who are infected with HIV. In phase I studies, a single vaccination with MVA85A, when administered at a dose of  $5 \times 10^7$  pfu intradermally, has been shown to be safe in both mycobacterially naïve individuals, those previously vaccinated with BCG and latently infected individuals. We will use  $1 \times 10^8$  pfu MVA85A intradermally in this study. A trial in BCG vaccinated subjects showed that the higher dose ( $1 \times 10^8$  pfu MVA85A) induced a significantly higher immune response but did not have a higher AE profile. In addition, because of a variable immune response, the trial in HIV positive subjects in the UK is split into two groups, the first getting  $5 \times 10^7$  pfu and the second getting  $1 \times 10^8$  pfu MVA85A. It has, therefore, been decided to use the higher dose in order to maximise the immune response whilst maintaining a good safety profile.

However, the T cell immunogenicity of MVA85A in HIV infected subjects who are not on ARV treatment is reduced compared to previous trials in HIV negative subjects.

There are two potential interventions we can do to improve the immunogenicity in this important target population where TB incidence is very high. First, it is possible that the immune response to MVA85A would be better in healthy, asymptomatic people who have a CD4 count of more than 300, but who have had their immune response reconstituted by ARV therapy. Therefore the rationale for adding a second arm to this study is to investigate the immunogenicity in a group of HIV infected subjects who are stable on ARV treatment.

It is important to determine which subjects have the best immune response to this vaccine, in order to select this group for inclusion in a proof-of-concept efficacy trial; this would maximize the prospects of demonstrating efficacy in this important target population.

The second possible way to enhance the immunogenicity in this group is to include a second MVA85A booster vaccine. In the first trial we conducted with MVA85A, we administered two doses of MVA85A, three weeks apart [37]. In this study we saw no impact of the second MVA85A immunization, and at such a short interval between doses, this is likely to be due to anti-vector immunity. Other studies using a recombinant MVA expressing malaria antigens have shown that boosting with the same vaccine one year after first dose is highly effective [31]. We would therefore like to boost subjects in this study in both the ARV and no ARV group with a second MVA85A immunization, administered ~6-12 months after primary immunization. Subjects already recruited into the first (no ARV) arm will be contacted, informed of the results so far and asked if they would be happy to receive a second immunization. They are clearly under no obligation to do so and this will be clearly explained to them. Subjects in the second (ARV) arm of this study will be consented to receive two immunisations with MVA85A, with ~6-12 months between the two doses. It is thought that by boosting ~6-12 months after the first vaccination that the anti-vector immunity will have waned and should not impact the potential boosting by the second MVA85A vaccination.

## Potential Risks and Benefits

### Potential risks

The general risks to participants in this Phase I study are associated with phlebotomy and with vaccination. The volume of blood drawn over the study period (652.5 +/- 20ml) should not compromise these otherwise healthy subjects. As vaccine-related side effects are believed to be related more to the vector used than the specific insert, it is expected that MVA85A will have a similar side effect profile to recombinant pox viruses encoding other antigens.

Potential risks include the following:

**Local reactions:** Mild tenderness, bruising, or fainting may result from venepuncture. An inflammatory reaction as manifested by redness, swelling, scaling and/or tenderness may occur at the site of vaccine injection. In previous studies using the vaccines MVA85A these local reactions have spontaneously resolved within weeks.

**Systemic Reactions:** Systemic reactions to immunization with vaccines using MVA as a carrier that could potentially occur include a flu-like illness with low-grade fever, chills and malaise. As with any other vaccine, temporary ascending paralysis, the Guillain-Barré syndrome (GBS) or immune mediated reactions that can lead to organ damage may occur. For influenza vaccines an excess of approximately 1 GBS case per million persons immunized has been observed. No cases were observed in people under 45 years of age. However, this has never been seen with these vaccines or vaccines containing any of their components. As with any vaccine, serious allergic reactions may occur.

**Allergic Reactions and Anaphylaxis:** As with any vaccine, allergic reactions are possible.

**TB specific risks:** There is a very small risk of a Koch reaction occurring when subjects latently infected with M.tb are vaccinated with MVA85A. All subjects will be closely monitored and followed up clinically. All volunteers found to be latently infected with M.tb will be offered treatment at the end of the trial, in accordance with the latest NICE guidelines (6 months of isoniazid).

**HIV specific risks:** There is a hypothetical risk of any vaccine causing a rise in viral load in HIV positive individuals. However in individuals established on ARVs this has not been seen with MVA vaccines [30]. A small number of HAART naïve individuals in Africa have also been vaccinated with a recombinant MVA with no significant or sustained rise in viral load or fall in CD4 count [32]. Volunteers will be monitored clinically together with regular monitoring of CD4 counts and viral loads. However, observed changes in CD4/viral load will have to be carefully interpreted in the context of a well-described natural fluctuation in these parameters. Any significant changes in these will be communicated to the volunteer's lead HIV physician forthwith and BHIVA guidelines (BHIVA treatment guidelines 2005) will be followed to determine the need to commence ARVs.

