#### **End of trial:**

The trial ends when the last volunteer has completed their last (twelve month) follow-up visit.

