**Table 2: Illustration of sequential events (screening and subsequent follow-up):**

| Visit number              | 1         | 2              | 3–8 | 9   | 10  | 11  | 12             | 12.1 ^ | 13–18            | 19  | 20  | 21  | 22  |
|---------------------------|-----------|----------------|-----|-----|-----|-----|----------------|-------------------|------------------|-----|-----|-----|-----|
| Day                       | Screening | 0              | 1–6 | 7   | 28  | 84  | 168
(+/-14) | 168-350           | 1–6 ◇ | 7   | 28  | 84  | 168 |
| Medical history           | √         | (√)            | (√) | (√) | (√) | (√) | (√)            | (√)               | (√)              | (√) | (√) | (√) | (√) |
| Physical examination      | √         | (√)            | (√) | (√) | (√) | (√) | (√)            | (√)               | (√)              | (√) | (√) | (√) | (√) |
| Vital signs °  | √         | √              | √   | √   | √   | √   | √              | √                 | √                | √   | √   | √   | √   |
| Urinalysis                | √         | √ † |     |     |     |     | √ † | √ †    |                  |     |     |     |     |
| Chest x-ray #  | √         |                |     |     |     |     |                |                   |                  |     |     |     |     |
| Venepuncture              | √*        | √*             |     | √*  | √*  | √*  | √*             | √*                |                  | √*  | √*  | √*  | √*  |
| Vaccination               |           | √              |     |     |     |     | √              | √                 |                  |     |     |     |     |
| Injection site inspection |           | √              | √   | √   | √   | √   | √              | √                 | √                | √   | √   | √   | √   |
| Adverse events documented |           | √              | √   | √   | √   | √   | √              | √                 | √                | √   | √   | √   | √   |

(√) If considered necessary (emphasizing any acute complaints)

^ Visit 12.1 is only required if a subject has been for their 6 month visit but was not revaccinated because the 6 month visit was prior to the second vaccination amendment

° Temperature (°C), blood pressure (mmHg), pulse rate (beats/minute)

† Women only for pregnancy test

# Performed if no available CXR within the last 3 months

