**Table 3: Temporal course of blood investigations:**

| Test/Timepoint  | Volume (ml)                | Scr   | 0     | 7     | 28    | 84    | 168 (+/- 14) | 12.1 ^ (168-350) | 7 ◇ | 28    | 84    | 168   | Total (ml) |
|-----------------|----------------------------|-------|-------|-------|-------|-------|--------------|-----------------------------|----------------|-------|-------|-------|------------|
| FBC             | 4                          | X     |       | X     |       | X     |              | X                           | X              |       | X     |       | 20-24      |
| BioChem         | 4                          | X     |       | X     |       | X     |              | X                           | X              |       | X     |       | 20-24      |
| HBV/HCV/β-HCG   | 4                          | X     |       |       |       |       |              |                             |                |       |       |       | 4          |
| HIV             | 4                          | X     |       |       |       |       |              |                             |                |       |       |       | 4          |
| CD4             | 4                          | X     | X     | X     | X     | X     | X            | X                           | X              | X     | X     | X     | 40-44      |
| Viral Load      | 8                          | X     | X     | X     | X     | X     | X            | X                           | X              | X     | X     | X     | 80-88      |
| HLA             | 4                          |       |       |       | X     |       |              |                             |                |       |       |       | 4          |
| Research Bloods | 20-30 (16-26 at screening) | X     | X     | X     | X     | X     | X            |                             | X              | X     | X     | X     | 216-326    |
| TOTAL           | –                          | 44-54 | 32-42 | 40-50 | 36-46 | 40-50 | 32-42        | 0-20                        | 40-50          | 32-42 | 40-50 | 32-42 | 364-484    |

◇ Note that the days from this point on are shown as days after the second vaccination

^ FBC, Biochemistry, CD4 and VL will be repeated for exclusion criteria evaluation if a subject has been for their 6 month visit but was not vaccinated because the 6 month visit was prior to the second vaccination amendment.

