**Booster vaccination:**

- For Group 1, if Day 168 visit is before Protocol 2.0 amendment, the second vaccination will be given between days 168-350 (visit 12.1). However, before the subject receives the second vaccination, all inclusion and exclusion criteria except number 5 (Prior receipt of a recombinant MVA or Fowlpox vaccine) will be reviewed to check if the subject is still eligible to receive the vaccine. At this additional visit, 20 ml of blood will be collected to perform FBC, Biochemistry, CD4 and VL tests. Urinalysis, to exclude glycosuria and significant proteinuria will be performed. If any exclusion criterion are met except number 5, the subject will not be revaccinated.
- For Group 2, the second vaccination will be given at Day 168 (+/- 14 days)
- A photograph of the vaccination site will be taken after revaccination. The subject will only be identifiable by a unique study number.

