**Subsequent follow-up visits**

Volunteers will be reviewed at 28 (+/- 4 days), 84 (+/- 7 days) and 168 days (+/- 14 days) after the second vaccination.

- An interim history will be taken and, if considered necessary a physical examination emphasizing any acute complaints will be performed.
- Vital signs will be checked and documented
- The injection site will be inspected and the largest diameter of any hardness or redness present, as well as the degree of pain reported for the time of the visit will be documented into the CRF.
- Solicited adverse events (local and general) that may have occurred since the volunteer was seen on day 7 post second vaccination will be documented in the CRF.
- Approximately 32-42 ml of blood will be collected for exploratory immunology, viral load and CD4 cell count on days 28, 84 and 168 after the second vaccination. On day 84 after the second vaccination only, haematology and biochemistry will also be performed; therefore, the blood volume will be 40-50 ml.

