#### **4. DEFINITE:**

- Reasonable temporal relationship to study product; and
- Event not readily produced by clinical state, environment, or other interventions; and
- Known pattern of response seen with other vaccines

Every AE observed or reported from the day of injection [Day 0] through to the end of the trial (twelve months after injection) will be recorded on the CRF.

All AEs will be followed until resolution of the symptom or laboratory change occurs, or until a non-study related causality is assigned.

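### The offer of latent TB treatment is tied to the last volunteer's last visit, so a subject who finishes early waits for others with no gain to the data

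*Protocol*

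**What the plan says.** The TB-specific paragraph of Potential risks (section 1) states that "All volunteers found to be latently infected with M.tb will be offered treatment at the end of the trial"; the treatment named is six months of isoniazid. Section 3 has its own heading for the end of the trial and defines it at trial level: "The trial ends when the last volunteer has completed their last (twelve month) follow-up visit".

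Section 5 sets each subject's schedule. The second dose is due at day 168 (+/- 14), or between day 168 and day 350 for Group 1 subjects whose day 168 visit came before the booster amendment. The final visit is "168 days (+/- 14 days) after the second vaccination". Tables 2 and 3 list nothing later.

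Section 8 (Adverse Events Assessment) uses the same term differently. Adverse events are collected from the day of injection, Day 0, "through to the end of the trial (twelve months after injection) will be recorded on the CRF".

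**The concern.** The offer is a safety provision for individuals, but it is tied to a date set by the slowest subject in the study. Holding treatment back during follow-up could be defended as keeping the immune readouts clean. Once a subject's own schedule is complete, that reason no longer applies.

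The subjects concerned are foreseeable. The exclusion criteria rule out TB disease and a chest film showing TB, but not latent infection. The secondary outcomes include responses to ESAT-6 and CFP-10, which the protocol itself describes as markers of TB infection. At stake is the timing of preventive treatment for HIV-positive people; the trial's endpoints are not at issue.

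**Working it through.** **Inputs**
- Second dose: day 168 (+/- 14), or up to day 350 at visit 12.1 (section 5, Booster vaccination).
- Last visit: 168 days (+/- 14) after the second dose (section 5, Subsequent follow-up visits; Table 2).
- Study duration: 24 months (Protocol Summary).
- Screening: up to 90 days before vaccination (section 4, Screening visit).
- Assumption: 24 calendar months = 730 days, counted from the first subject's Day 0. Accrual is not stated, so the true trial end is unknown.

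**Step 1. Each subject's own last visit** = day of second dose + 168.
- Boost at day 168: 168 + 168 = day 336. With both windows at their limits: 154 + 154 = 308 to 182 + 182 = 364.
- Boost at day 350: 350 + 168 = day 518 (504 to 532 with the window).

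Section 3 labels the last visit as the twelve-month one. The Table 2 footnote calls day 168 the six-month visit ("Visit 12.1 is only required if a subject has been for their 6 month visit"), so a protocol month is 168 / 6 = 28 days and twelve months is 12 x 28 = day 336. The label is therefore reproduced exactly for a day 168 boost, and not for a day 350 boost.

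**Step 2. Is anything sampled after that visit?** No. In Tables 2 and 3 the final column is day 168 after the second dose, and the Table 3 footnote confirms the clock: "Note that the days from this point on are shown as days after the second vaccination".

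**Step 3. Wait beyond the subject's own last visit, under the section 3 definition** = trial end - own last visit.
- First subject, boost at day 168: 730 - 336 = 394 days. With visit windows: 730 - 364 = 366 to 730 - 308 = 422.
- First subject, boost at day 350: 730 - 518 = 212 days.
- If the 24 months start at a screening visit 90 days before Day 0: 730 - 90 - 336 = 304 days (day 168 boost).
- Last volunteer to finish: 0 days.

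**Step 4. The section 8 use of the term**, counted from the Day 0 injection.
- In calendar months the date is day 365. Day 168 boost: 365 - 336 = 29 days after the last visit. Day 350 boost: 518 - 365 = 153 days before it.
- In 28-day months the date is day 336. Day 168 boost: 0 days. Day 350 boost: 518 - 336 = 182 days before it.

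**The case against.** The strongest reply is that the sentence sits in a summary of risks and could be read as the end of that volunteer's participation. It bars no earlier treatment, and the inclusion criteria already require that the investigators may talk to the subject's HIV physician. In addition, the protocol schedules no date for diagnosing latent infection, so the day counts are not delays from a known diagnosis.

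The points about routine care and diagnosis stand, and they limit the weight of the matter. The benign reading does not remove it, because section 3 defines the term under its own heading and the definition is a trial-level date.

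A reader might also infer stronger claims that the documents do not support:

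- *That neither use of the term matches a subject's own last visit.* For a day 168 boost the section 8 date nominally is that visit.
- *That the site has two competing dates for the offer.* Section 8 governs adverse event recording and says nothing about treatment.
- *That section 8 might mean the second injection.* Its sentence starts from the injection on Day 0.
- *That subjects without a second dose have a long guaranteed wait.* Such subjects can exist: the booster is voluntary for those already recruited to Group 1, and for visit 12.1 "If any exclusion criterion are met except number 5, the subject will not be revaccinated". No separate schedule is given for them, however. A last visit at about day 168 would be an inference, and sections 3 and 8 both speak of twelve months without exception. A minimum wait would further need Group 2 to have enrolled after the amendment, which is implied but not stated.
- *That the delay carries a calculable TB risk.* The background quotes 10% a year for latently infected people who become immunosuppressed. Nothing shows that this rate applies to asymptomatic subjects with CD4 counts above 300.

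**Conclusion.** The point holds in a limited form. Read through the protocol's own definition, the offer waits for the last volunteer's last visit, and any wait past the subject's own last visit brings the trial nothing.

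The size cannot be fixed from the protocol. It is zero for the last volunteer and about 394 days for a first subject boosted at day 168, if the trial runs 24 calendar months from that subject's Day 0. On the same assumption it is 212 days for a first subject boosted at day 350. How many subjects would be found latently infected, and when, is not stated.

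No endpoint is affected and routine care is not blocked. This is a worthwhile safety correction that should be made because it is cheap and specific; it does not undermine the design.

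The section 8 wording is secondary. For a late-boosted subject, adverse event recording as written there would stop about 153 days (calendar months) before the last scheduled visit, so the term is badly chosen in that place.

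**What to change.** In Potential risks, replace the timing with: volunteers found to be latently infected will be offered treatment, or referred to their HIV physician for it, no later than their own last study visit. Add that if the physician starts treatment earlier, the start date is recorded and is taken into account in adverse event causality and in the summaries of immune responses.

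Keep the term for trial end only in the section 3 sense. In section 8, use a separate term for the subject's own end of follow-up: the later of twelve months after Day 0 and the last scheduled visit, so that adverse event recording is not shortened for anyone.

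The cost is a wording amendment, with the sponsor agreement and ethics approval that section 14 requires, and a matching change to the information sheet if it repeats the statement. No visit, sample or endpoint changes. The one real cost is that treatment begun during follow-up adds another possible cause when adverse events, the primary outcome, are attributed, and it may affect immune readouts; hence the recorded start date. An offer made at the last visit leaves the scheduled samples untouched.
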